## Abstract

**Objective:**

The purpose of this double-blind, randomised, placebo-controlled, adaptive design trial with frequent interim analyses is to determine if Australian Indigenous children, who receive an additional (third) dose of human rotavirus vaccine (Rotarix, GlaxoSmithKline) for children aged 6 to < 12 months, would improve protection against clinically significant all-cause gastroenteritis.

**Participants:**

Up to 1000 Australian Aboriginal and Torres Strait Islander (hereafter Indigenous) infants aged 6 to < 12 months will be recruited from all regions of the Northern Territory.

**Interventions:**

The intervention is the addition of a third scheduled dose of human monovalent rotavirus vaccine.

**Co-primary and secondary outcome measures:**

ORVAC has two co-primary outcomes: (1) anti-rotavirus IgA seroconversion, defined as serum anti-rotavirus IgA ≥ 20 U/ml 28 to 55 days post Rotarix/placebo, and (2) time from randomisation to medical attendance for which the primary reason for presentation is acute gastroenteritis or acute diarrhoea illness before age 36 months. Secondary outcomes include (1) change in anti-rotavirus IgA log titre, (2) time from randomisation to hospitalisation with primary admission code presumed or confirmed acute diarrhoea illness before age 36 months, (3) time from randomisation to hospitalisation for which the admission is rotavirus confirmed diarrhoea illness before age 36 months and (4) time from randomisation to rotavirus infection (not necessarily requiring hospitalisation) meeting the jurisdictional definition before age 36 months.

**Discussion:**

A detailed, prospective statistical analysis plan is presented for this Bayesian adaptive design. The plan was written by the trial statistician and details the study design, pre-specified adaptative elements, decision thresholds, statistical methods and the simulations used to evaluate the operating characteristics of the trial. As at August 2020, four interim analyses have been run, but no stopping rules have been triggered. Application of this SAP will minimise bias and supports transparent and reproducible research.

**Trial registration:**

Clinicaltrials.gov NCT02941107. Registered on 21 October 2016

**Original protocol for the study:**

10.1136/bmjopen-2019-032549

## Background

Despite the introduction of rotavirus vaccine into the childhood vaccination schedule in 2006, Northern Territory Indigenous children remain more than 20 times more likely to be hospitalised with rotavirus gastroenteritis than non-Indigenous children in other Australian states and territories [1]. Data from remote communities in the Northern Territory suggests that 77% of children have at least one documented episode of clinic attendance for diarrhoea before their first birthday, with a median of three (IQR 1–5) clinical presentations for diarrhoea per child in the first year of life [2].

The current vaccination schedule with Rotarix is at 2 and then 4 months of age. We hypothesise that the routine addition of a third scheduled dose of Rotarix for NT Indigenous infants, administered between 6 months and less than 12 months old, will improve protection against clinically important rotavirus gastroenteritis.

This statistical analysis plan (SAP) provides a priori specification of the decision-making rules and the statistical methods to be used. It is intended to disseminate practical knowledge on adaptive trials to trialists that are new to these designs. The SAP was prepared after data collection had commenced, but prior to observing any of the data. The coordinating principal investigator ([name]) was responsible for approving and signing off the SAP, and the document has also been reviewed and approved by an independent data monitoring safety board (DMSB). The SAP is consistent with the CONSORT 2010 Statement [3] and further guidelines [4–6] and supports transparent and reproducible research.

As at August 2020, four interim analyses have been run, but no stopping rules have been triggered.

## Adaptive designs

While fixed design clinical trials are conceptually straightforward, they suffer from rigidity and frequently end with inconclusive results [7, 8]. Contrastingly, adaptive designs (ADs) allow for pre-specified adaptations that modify the design as the trial progresses and as data is accumulated [9].

Typical adaptations include dynamic changes to sample size, dropping treatment arms for futility, response adaptive randomisation, seamless phase II/III trial transitions, study population enrichment and early stopping rules [10] that are triggered under predefined conditions [11]. Consequently, ADs may be completed sooner, cost less to run, reduce the number of patients exposed to inferior treatments and provide more clinically relevant data than fixed designs [12]. However, ADs are not without their own limitations. The processes associated with obtaining funding, planning and designing adaptive trials are complex and can require more effort and time than traditional trials [8]. Furthermore, developing simulations [13] to explore the frequentist operating characteristics (e.g. type I error and power) requires specialist staff and/or consulting services, custom software infrastructure and high-performance computing facilities [7].

Historically, ADs and platform trials (a variant of an adaptive trial) have generally been implemented in phase I and II settings in the USA, with many originating from the University of Texas MD Anderson Cancer Center [11, 14, 15]. However, interest in ADs is growing and they are now being deployed and evaluated in phase III (e.g. [16–18]) and IV settings [9, 19]. In early 2016, the REMAP-CAP (Randomised, Embedded, Multifactorial Adaptive Platform trial for Community-Acquired Pneumonia) trial, an embedded platform trial run jointly in Europe, Australia and New Zealand, commenced. REMAP-CAP has served as a catalyst, motivating Australian trialists to raise funds, develop capacity and become involved in adaptive trials to answer their research questions. Examples include BEAT CF [20] and GBM Agile [21]. The ORVAC trial is one of several Bayesian ADs that are in development at the Telethon Kids Institute in collaboration with Berry Consultants.

## ORVAC study design

ORVAC is a pragmatic, investigator-led, double-blind, randomised, placebo-controlled Bayesian adaptive clinical trial testing a third scheduled dose of Rotarix rotavirus vaccine (versus usual care) in Australian Indigenous infants to improve protection against clinically important gastroenteritis. It has the following key features:
Double-blind, randomised, placebo-controlled trial (neither the outcome observer nor participant’s caregivers know the treatment status);Non-fixed sample size up to 1000 participants (up to the first 250 with venous sampling) based on Bayesian stopping rules (minimum sample size of 70 for predicting futility);Fixed 1:1 parallel group enrolment into the active and control arm throughout the trial;Frequent interim analyses;Evaluation of intervention effects in the Darwin urban region compared to remote/very remote regions; andStudy participation is from randomisation until the end of follow-up at 36 months of age.

### Adaptive elements

The adaptive elements all relate to sample size. Enrolment will continue up to the maximum sample size unless one of the following criteria for a statistical trigger is met at an interim analysis:
Stop venous sampling because the treatment arm shows overwhelming evidence of an increase in seroconversion.Stop for futility, ceasing the trial before the maximum sample size is reached because the probability of observing a beneficial treatment effect is very small, even if the trial were continued to its maximum sample size.Stop for expected success, ceasing the trial before the maximum sample size is reached because:
Futility in both the immunological and clinical outcome is very unlikely; andThe treatment group shows overwhelming evidence of an increase in the median time to medical attendance for which the primary reason for presentation is presumed or confirmed acute gastroenteritis or acute diarrhoea illness.

Futility and expected success are tested sequentially, which implies that if we establish futility in either the immunological or clinical outcome, then we will not test for expected success.

## Trial population

ORVAC has two population subgroups: (1) children who normally reside in a major city, an inner or outer regional area and (2) children residing in remote or very remote areas according to the Australian Government Department of Health Australian Standard Geographical Classification-Remoteness Area (ASGC-RA) system. While baseline characteristics for immunological status and median time to medical attendance/hospitalisation are not well understood for this population, comparable settings have an RV vaccine efficacy of around 50%. However, in the NT Indigenous population, protection has been noted to wane after the first year of life, estimated to fall to a rate of only 10% [22]. Estimates for the rate of hospitalisations due to acute gastroenteritis are also highly variable with median times to hospitalisations reported to be between 15 and 40 months from birth [1].

The clinical data from this trial will be analysed and reported on an intention-to-treat (ITT) basis with all randomised participants contributing to the analysis of the co-primary endpoints. Specifically, for the ITT analysis:
Patients will be analysed in the group they were allocated to;Patients not receiving Rotarix/placebo will be retained;False inclusions will be retained;Protocol deviations will not result in exclusion; andThe potential effect of missing values will be examined (see later).

We will also produce companion analyses on a per-protocol (PP) basis using the subset of participants that completed without protocol violation.

## CONSORT diagram

We will prepare an expanded CONSORT diagram suitable for a parallel two-armed adaptive trial. We will record the start and end dates of accrual, the flow of participants through the study including the completeness of follow-up as per the CONSORT statement [23]. We will note participants enrolled and randomised and eligibility for analyses.

## Study objectives and outcomes

The purpose of this study is to determine if Indigenous children who receive an additional dose of Rotarix between the ages of 6 and 12 months will have an increased anti-rotavirus serum IgA seroconversion and an increase in the time to medical attendance due to gastroenteritis in the first 3 years of life, compared to those who receive placebo.

### Co-primary

The primary objective is quantified through a clinical and an immunological outcome designed to measure the clinical effectiveness of an additional scheduled dose and any change in the immune response.

The immunological outcome is anti-rotavirus IgA seroconversion, defined as serum anti-rotavirus IgA ≥ 20 U/ml at 28 to 55 days post Rotarix/placebo among infants with anti-rotavirus serum IgA < 20 U/ml prior to administering the third dose.

The clinical outcome is the time from randomisation to first medical attendance (hospitalisation, emergency department presentation, medical clinic presentation) for which the primary reason for presentation is presumed or confirmed all-cause acute gastroenteritis or acute diarrhoea illness between randomisation and age 36 months.

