#### Immunological co-primary outcome

The immunological outcome will be modelled using logistic regression including a covariate for treatment status (control arm coded as 0, treatment coded as 1). Denoting *y*_*i*_ as the seroconversion status, *π*_*i*_ as the probability of seroconversion and trt_*i*_ as an indicator variable for group membership for individual *i*, in the simplest case, we have:
1$$\begin{array}{*{20}l} y_{i} &\sim \text{Bin}(1, \pi_{i}) \end{array} $$

2$$\begin{array}{*{20}l} \text{logit}(\pi_{i}) &= \beta_{1} + \beta_{\text{trt}} \times \text{trt}_{i} \end{array} $$

However, we will also fit additional models that adjust for locality (urban versus remote), locality by treatment interaction, sex of participant, breast-feeding status in the 7 days prior to enrolment and community-specific indicators for gastroenteritis outbreaks.

We will use independent Student *t* distribution priors with location zero and scale 3 with 7 degrees of freedom that are recommended for general purposes [27, 28]. These priors imply
The parameters are as likely to be positive as they are to be negative;The intercept is consistent with baseline log-odds between − 10 and 10; andA unit change in any covariate would be unlikely to exceed an absolute change of 5 on the log-odds scale.

We note that these priors are similar to normal priors, which are also suitable for logistic regression, but the Student *t* has slightly heavier tails [28]. The Student *t* priors are considered weakly informative and produce stable, moderately regularised and robust estimates. When using the Student *t* priors, it is recommended that binary independent variables are shifted to have a mean of zero and differ by one and that continuous independent variables have a mean of zero and a standard deviation of 0.5 [27]. Therefore, we will adopt this transformation, which puts all the input variables onto the same scale.

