We will calculate the probability that the log odds ratio (*β*_trt_) is greater than zero. If this probability exceeds 0.97, chosen by simulation to control the type I error, we will conclude a successful treatment effect of increased probability of seroconversion in the treatment arm. In notation, we conclude a treatment effect has been demonstrated if $\mathbb {P}(\beta _{\text {trt}} > 0)> 0.97$. We will report both absolute values of the proportion of participants that seroconverted in each arm and the treatment effect size as a difference in proportions and as odds ratios.

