## Evaluation of operating characteristics

Except for the simplest of cases, the operating characteristics for a Bayesian adaptive trial are analytically intractable. Therefore, these are usually estimated by Monte Carlo methods, which are a general purpose tool for optimisation and integration problems [45]. In the context of exploring the operating characteristics of a given trial, the idea is to formulate a data generating process (DGP) that represents expected and plausibly extreme outcomes for the actual trial. However, as is the case here, it may be necessary to simplify the data generating process and/or analysis approach in order to be able to run the simulations within a workable timeframe. Using the assumed DGP, trial data can be simulated many times and the resulting ‘virtual trials’ are analysed using methods described shortly. Various characteristics of the DGP can then be derived. For example, the expected type I error (false positive rate) is derived from data that are generated under a null effect configuration and estimated from the proportion of times that we falsely detect a difference between the treatment arms in the final analysis.

We have examined the operating characteristics of the ORVAC trial in more than 300 scenarios using Monte Carlo simulation of the parameter space associated with a representative data generating, sampling and modelling process. For the immunological endpoint, seroconversion was modelled via a series of independent Bernoulli trials with control arm probabilities of seroconversion (the baseline seroconversion rate) between 0.1 and 0.7 and a change of probability of seroconversion in the treatment arm between 0 (the null case) and 0.15 above the baseline rate. Additionally, we modelled information delays associated with processing the immunological endpoint of 0.5 and 0.7 months. For the clinical endpoint, we modelled time to event as an exponentially distributed random variable. The control arm median time to event was set at 20–50 months and a change in the median time to event varied between 0 (the null case) and 15 months. Event times were censored at 36 months of age. We modelled accrual using a Poisson process generating approximately 30 and 50 participants per quarter. Age at vaccination was modelled using a uniform distribution with lower and upper bounds of 6 and 12 months respectively. The co-primary endpoints were modelled as independent random variables.

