**Fig. 8 Fig8:**
[figure not shown]
Expected sample size (venous samples) assessed on immunological outcome over a range of baseline values, effect sizes and accrual rates

The clinical and immunological outcome are analysed independently. For the clinical outcome, power increases monotonically as a function of increasing effect size and lower baseline median time-to-event scenarios. For a baseline median time to event of 35 months, power climbs from 50 to 75% as the difference between the median time to event in the two arms increases from 10 to 15 months. At a baseline time to event of 20 months, the power to detect a 10-month difference is over 70%. Power was relatively insensitive to the accrual rates and information delays that we examined.

For the immunological outcome, power is largely independent of the clinical outcome configuration. For a baseline probability of seroconversion of 0.4, while the power to detect a 0.1 difference in probability of seroconversion is only around 40%, this increases to around 70% to detect a difference of 0.15. However, when the baseline probability of seroconversion is 0.1, the power to detect a 0.1 difference is in excess of 60% and to detect a 0.15 difference is well in excess of 80%.

The probability of expected success increases as a function of the difference between the median time to event in the treatment versus control arm. When the difference between the probability of seroconversion between the treatment and placebo arms is 0.05, the probability of expected success is only around 0.2. However, as the difference in the seroconversion probabilities increases, the probability of expected success becomes increasingly likely.

The probability of stopping for futility is dependent on both the clinical and immunological outcomes. For a difference between the median time to event equal to 5 months, the probability of futility is up to 0.7. However, as the difference between the median time to event and probability increases, the probability of futility drops to less than 0.1.

The probability of stopping venous sampling before reaching the maximum of *n* = 250 is only around 0.2 when the difference in the probability of seroconversion between the two arms is 0.05. However, this increases rapidly as the difference between the groups increases and is up to 0.8 when the difference in the probability in the two arms is 0.15.

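### The adjusted seroconversion models omit pre-dose IgA, which every infant in that analysis must have and which predicts crossing the 20 U/ml line

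*SAP article*

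**What the plan says.** Under Co-primary, the SAP article gives the immunological outcome as seroconversion, "defined as serum anti-rotavirus IgA ≥ 20 U/ml at 28 to 55 days post Rotarix/placebo among infants with anti-rotavirus serum IgA < 20 U/ml" before the dose. One value is both the entry limit and the response limit.

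Under Immunological co-primary outcome, the basic model is a logistic regression on treatment alone. The section then says "we will also fit additional models that adjust for locality (urban versus remote), locality by treatment interaction, sex of participant", and completes the list with recent breast-feeding and community outbreak indicators. Pre-dose IgA is not on it. The same section has continuous covariates centred and scaled to a standard deviation of 0.5. Its success rule reads "If this probability exceeds 0.97, chosen by simulation to control the type I error", and it promises the proportion converting in each arm, their difference and odds ratios.

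Change in log IgA titre, which uses no cut-off, is a secondary outcome analysed by robust linear regression (Table 1).

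**The concern.** A threshold outcome discards the size of the rise, so the starting value carries much of the remaining information on who will cross. An infant at 18 U/ml needs a 20/18 = 1.11-fold rise; one at 2 U/ml needs 20/2 = 10-fold. If responders rise on average by 0.9 log10 (10^0.9 = 7.9-fold), a typical responder starting at 2 U/ml reaches about 16 U/ml and is not counted, while an infant at 18 U/ml may cross through measurement variation alone. Both happen on vaccine and on placebo.

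Randomisation keeps the comparison fair, so no bias is at issue. What is at stake is sensitivity. The SAP's own power for this outcome is modest in places: at a control rate of 0.4, power for a 0.1 difference "is only around 40%, this increases to around 70% to detect a difference of 0.15". A prognostic covariate that is already measured is an inexpensive way to gain some of it back.

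**Working it through.** **Inputs from the SAP.** Venous sampling is planned for "up to the first 250 with venous sampling". Allocation is "Fixed 1:1 parallel group enrolment into the active and control arm throughout the trial", so 250/2 = 125 per arm. The posterior threshold of 0.97 corresponds to a one-sided 0.03 test at fixed size (critical value 1.881). The design simulations used "control arm probabilities of seroconversion (the baseline seroconversion rate) between 0.1 and 0.7".

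**Step 1: reproduce the stated power.** With z = (p1 − p0)/√[(p0(1 − p0) + p1(1 − p1))/125] and power = Φ(z − 1.881):

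| Control v vaccine | z | Power | SAP (Sample size, power and expected success) |
|---|---|---|---|
| 0.4 v 0.5 | 0.10/0.0626 = 1.597 | 39% | around 40% |
| 0.4 v 0.55 | 0.15/0.0624 = 2.402 | 70% | around 70% |
| 0.1 v 0.2 | 0.10/0.0447 = 2.236 | 64% | above 60% |
| 0.1 v 0.25 | 0.15/0.0471 = 3.184 | 90% | well above 80% |

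The stated figures reproduce.

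**Step 2: the gain from pre-dose log IgA.** The SAP gives no titre distribution, assay precision or within-child variation, so all of the following are assumptions:

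- True log10 titre is normal with SD 0.7 or 1.0, placed so that 30% or 50% of all infants truly lie at or above 20 U/ml.
- Each reading has noise SD 0.05, 0.10, 0.15 or 0.20 log10. This makes 2 × 2 × 4 = 16 settings.
- 250 infants reading below 20 U/ml are split 125 per arm. True response is 10% on placebo and 25% on vaccine, with a mean rise of 0.9 log10 (SD 0.3).
- The analysis is logistic with weakly informative priors and a single look. Success is P(β_trt > 0) > 0.97, with and without pre-dose log IgA scaled to SD 0.5.

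A run with 1,000 trials per setting gave about 3 to 7 points more power in every setting. A repeat with 2,000 trials per setting gave 3.3 to 6.4 points. Examples from the repeat:

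| Titre SD | Truly ≥ 20 U/ml | Noise SD | Treatment only | With pre-dose log IgA |
|---|---|---|---|---|
| 0.7 | 30% | 0.05 | 62.9% | 66.4% |
| 1.0 | 50% | 0.15 | 42.0% | 47.6% |
| 0.7 | 50% | 0.20 | 44.3% | 50.7% |

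With equal response rates (10% in both arms), the success rate was 0.020 to 0.034 with the covariate and 0.018 to 0.032 without it (Monte Carlo SE about 0.004). There is no sign of inflation.

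The absolute powers are not comparable with Step 1, because 10% v 25% are true-response rates. The crossing rates differ from them (in the first row, 8.3% v 17.8%): some responders start too low to cross and some non-responders cross by noise.

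**Step 3: sensitivity to the rise.** With a mean rise of 1.5 log10 (about 32-fold), nearly all responders cross wherever they start, and the gain falls to about 1 to 5 points. It stayed positive in all 16 settings.

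**The case against.** The strongest reply is that nothing in the plan is wrong. The definition is clear and coherent, every threshold outcome treats a small crossing like a large one, and the log-titre secondary outcome already separates them. This largely stands: the point is an improvement, and its size depends on variability that the SAP does not report. The log-titre outcome is only partial cover, since the SAP calls the secondary objectives exploratory and does not link its immunological conclusion to them.

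A second reply is that adjustment changes what the odds ratio means, because odds ratios are non-collapsible. That also stands. It is met by continuing to report the unadjusted proportions and their difference.

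A third limit is that the immunological section, unlike the clinical one, does not say that the 0.97 rule is read from an adjusted model. The gain reaches the success decision only where it is. Otherwise it sharpens a supporting analysis.

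A reader might go further and infer that noise crossings make the stated power too high. Adding a 5% false-crossing rate f by p + (1 − p)f turns 0.1 v 0.2 into 0.145 v 0.24, and power falls from 64% to 52%. For 0.4 v 0.55 it falls from 70% to 65%. But this treats the SAP's rates as free of noise. They are more naturally read as rates on the outcome as defined, so placebo crossings from any cause are already inside the 0.1 to 0.7 range. On that reading the stated power is right, as Step 1 shows.

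**Conclusion.** Pre-dose log IgA belongs in the adjusted seroconversion models. It is available for every infant in the analysis, it predicts crossing, and it is absent from the list. The gain is about 3 to 7 points of power under the Step 2 assumptions (mean rise about 8-fold) and about 1 to 5 points if the mean rise is about 32-fold, with false positives unchanged. The true size cannot be known from the SAP.

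Three stronger readings are not supported. The 20 U/ml definition is not an error: expected noise is equal in the two arms, so it neither favours vaccine nor raises type I error. The stated power is not shown to be overstated. More frequent futility stopping is also not shown: it would need the same noise-free reading of the design rates, and no calculation here establishes it. Absence of assay precision or repeat testing from this article is not a finding, since such detail commonly sits in the protocol or laboratory manual.

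**What to change.** In Immunological co-primary outcome, add pre-dose log IgA to the covariates of the adjusted seroconversion models at the final analysis, centred and scaled as the section already provides for continuous covariates. State one fixed rule for values below the assay's detection limit. Keep the 20 U/ml definition, the 0.97 threshold and the treatment-only interim models unchanged. Keep the unadjusted proportions and their difference in the report, and label the adjusted odds ratio as conditional.

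Optionally, report a descriptive sensitivity analysis that also requires a minimum fold-rise, with the multiple fixed blind to arm. The immunological conclusion should not depend on it: four interim analyses had been run by August 2020, no operating characteristics exist for such a rule, and it would drop genuine responders with small rises.

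The cost is a few lines of SAP text and one more covariate on data already collected, with no new blood samples or participants. Because the statistician running the interims is unblinded, blinded investigators should make and date the decision.
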